**Secondary Endpoints:**

Proportion of Grade 3+ acute (up to 3 months) and early late (3–6 months) toxicity rates, comparing dose-escalated and standard radiotherapy cohorts.

Patient reported quality of life scores, comparing dose-escalated and standard radiotherapy cohorts.

Loco-regional control rates at 12 and 24 months, overall survival, and cancer specific survival; comparing dose-escalated and standard radiotherapy cohorts.

**Exploratory Endpoints:**

Safety and feasibility of research biopsy at #10 of radiotherapy.

Feasibility of molecular profiling studies (including panel-based/WES DNA sequencing, bulk RNA profiling and spatial analysis of RNA expression and protein on baseline and #10 biopsies.

Feasibility of identifying circulating biomarkers (including ctDNA, metabolites, circulating immune cell populations and cytokines/chemokines) from blood, plasma and/or saliva.

### Statistics

2.6

A sample size of 20 patients will be targeted. Using a one-sided significance level of 0.05 and 80% power, the true success rate would need to be approximately 0.76, to demonstrate a success rate of greater than 50%. For the primary endpoint of feasibility, the proportion of patients able to complete DW-MRI guided response adapted radiotherapy will be reported with an exact 95% confidence interval. For the secondary safety analysis, the proportion of dose escalated patients experiencing grade III or IV RT-related toxicities will be compared with standard treatment patients using an odds-ratio with an exact 95% confidence interval. The time of onset and duration of severe toxicities, as well as the number of patients missing one or more treatment days, will also be reported. The number of patients achieving loco-regional control at 6-months follow-up will be reported, along with an odds ratio for the comparison of groups and an exact 95% confidence interval. Overall survival and cancer-specific survival will also be summarised at 6-months follow-up, presented with Kaplan-Meier plots and log -rank tests.

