**Primary Endpoint:**

The proportion of patients able to complete DW-MRI guided response-adapted radiotherapy with a target of 50%.

The benchmark of 50% was a pragmatic decision, selected to be permissive enough to avoid prematurely abandoning a potential new treatment strategy, yet with a predefined threshold to indicate futility of further evaluation. It allows for an important activity of both the study and the R-IDEAL framework, optimisation of the novel workflow.

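### With 20 patients, 80% power at one-sided 0.05 needs a true completion rate of about 0.80, not 0.76; at 0.76 the exact power is about 66%

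*Protocol article*

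**What the plan says.** The primary endpoint in section 2.5 is "The proportion of patients able to complete DW-MRI guided response-adapted radiotherapy with a target of 50" per cent. The same place calls that benchmark pragmatic and treats it as a threshold for futility.

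Section 2.6 gives the design calculation:

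- Size: "A sample size of 20 patients will be targeted".
- Error rates: "Using a one-sided significance level of 0.05 and 80% power".
- Detectable rate and purpose: "the true success rate would need to be approximately 0.76, to demonstrate a success rate of greater than 50" per cent.
- Analysis: the completion proportion "will be reported with an exact 95% confidence interval".

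The section names no hypothesis test, no cutoff on the number of completers, and no approximation behind the 0.76.

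**The concern.** Four quantities are stated together: n = 20, one-sided alpha 0.05, power 80% and a true rate of 0.76 against 50%. With only 20 patients the number of completers is coarsely discrete, and the attainable error rates move in large steps. A formula that treats the count as continuous can then promise a combination that no actual cutoff delivers. The analysis is also to use an exact interval, so the design figure and the planned report may rest on different methods.

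This is the article's only power statement and it concerns the primary endpoint. If it is optimistic, the chance of an inconclusive result is larger than readers are told. There is also a borderline result, 14 of 20, where the approximation would declare success while the published interval still included 50%.

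**Working it through.** **Inputs.** n = 20, one-sided alpha = 0.05, power = 80%, alternative rate about 0.76 and analysis by exact interval are from section 2.6. The null rate p0 = 0.50 is from section 2.6 and matches the benchmark in section 2.5.

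**Step 1: reproduce the stated 0.76.** The one-sample normal approximation, with null variance for alpha, alternative variance for power and no continuity correction, solves

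p1 − p0 = z(0.95)·√[p0(1 − p0)/n] + z(0.80)·√[p1(1 − p1)/n].

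- First term: 1.645 × √(0.25/20) = 1.645 × 0.1118 = 0.1839.
- Second term at p1 = 0.764: 0.8416 × √(0.764 × 0.236/20) = 0.8416 × 0.0950 = 0.0799.
- Sum: 0.2638, so p1 = 0.764, which agrees with the stated figure.

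The arcsine version also gives 0.764. With a continuity correction the answer is already 0.786.

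**Step 2: find the cutoff that holds alpha.** Under Binomial(20, 0.5), where 2^20 = 1,048,576:

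- P(X ≥ 15) = (15,504 + 4,845 + 1,140 + 190 + 20 + 1)/1,048,576 = 21,700/1,048,576 = 0.0207.
- P(X ≥ 14) = (21,700 + 38,760)/1,048,576 = 60,460/1,048,576 = 0.0577.

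Fourteen of 20 exceeds 0.05, so 15 of 20 is the lowest cutoff that respects the stated level.

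**Step 3: check against the planned interval.** Clopper–Pearson lower limits:

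| Completers | Two-sided 95% | One-sided 95% |
|---|---|---|
| 14/20 | 45.7% | 49.2% |
| 15/20 | 50.9% | 54.4% |

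On either reading of the interval, 50% is excluded only from 15 of 20.

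**Step 4: exact power.** P(X ≥ r) at the true rate p, with n = 20:

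| Cutoff | Type I error at 0.50 | Power at 0.76 | Power at 0.80 | True rate for 80% power |
|---|---|---|---|---|
| ≥ 14/20 | 0.0577 | 0.816 | 0.913 | 0.755 |
| ≥ 15/20 | 0.0207 | 0.657 | 0.804 | 0.799 |

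The risk of a miss at a true rate of 0.76 is therefore 1 − 0.657 = 0.343, against the 0.20 implied.

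**Step 5: what 0.76 would need.** Taking for each n the lowest cutoff with exact alpha of at most 0.05:

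| n | Cutoff | Alpha | Power at 0.76 |
|---|---|---|---|
| 20 | 15 | 0.0207 | 0.657 |
| 21 | 15 | 0.0392 | 0.778 |
| 22 | 16 | 0.0262 | 0.738 |
| 23 | 16 | 0.0466 | 0.834 |
| 24 | 17 | 0.0320 | 0.801 |
| 25 | 18 | 0.0216 | 0.765 |
| 26 | 18 | 0.0378 | 0.850 |

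Every n from 26 to 39, the largest checked, also reaches 80%.

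**The case against.** The best defence is that 0.76 is not a slip. It is the answer from a standard formula, it is described as approximate, and no exact test is named: the word exact is attached only to the interval used for reporting. Under the score test that belongs to that formula, 14 of 20 gives z = 0.20/0.1118 = 1.79, above 1.645, so 14 would count as success and the true power at 0.76 would be 81.6%. A mid-p test also rejects at 14 of 20 (0.0207 + 0.0370/2 = 0.039). On that reading the cost is not 14 points of power but 0.8 points of type I error (5.8% against 5%). The defence adds that the study is a small feasibility study with a deliberately permissive benchmark, and that 0.76 was worked back from n = 20 and did not set n.

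Part of this stands. The figure has a traceable origin, the design is reasonable for its purpose, and neither the estimate nor its interval changes. It does not rescue the sentence, though. The stated level is 0.05, and no cutoff on 20 patients that holds it has more than 65.7% power at 0.76, whichever test is named. The 14-of-20 rule gets its power by exceeding that level, and at 14 of 20 the exact interval, the only method given for this endpoint, includes 50%. If instead the decision were simply whether the observed proportion reaches 50%, the power statement would describe nothing the trial does. An unseen analysis plan may name a test, but it cannot make these four figures hold together.

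**Conclusion.** The concern holds. At n = 20 and one-sided 0.05, power at a true completion rate of 0.76 is 65.7% instead of 80%. The rate needed for 80% power is 0.799 instead of 0.76, and the attained type I error is 2.1%.

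This assumes that all 20 patients count in the denominator, that outcomes are independent with a common completion rate, and that the 0.05 level is to be strictly held. If a true error of 5.8% were accepted, 14 of 20 would give 81.6% power at 0.76, but the article does not say so and its interval would contradict that call. The consequence is limited to the stated operating characteristics, which matter mainly for reading a result near 14 or 15 completers.

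**What to change.** Keep 20 patients and replace the power sentence with something like: *Using an exact one-sided binomial test (nominal level 5%, attained level 2.1%), a completion rate above 50% is demonstrated if at least 15 of 20 patients complete. Power is 80% if the true rate is about 0.80 and about 66% if it is 0.76.*

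Because this puts a cutoff of 15/20 = 75% observed next to a 50% futility benchmark, add a clause saying how the two relate: which result demonstrates a rate above 50%, and which result would stop further evaluation.

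If 80% power at 0.76 is to be kept, the sample must grow: 23 patients (at least 16 completers, alpha 0.0466, power 0.834) or 24 (power 0.801). Twenty-five falls short at 0.765, and 26 and above suffices as far as was checked.

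The restatement costs one or two sentences and a less favourable detectable rate. The alternative costs at least three more patients.

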### Assessments and endpoints

2.5

The schedule of study assessments is detailed in Table 3 below. The following assessments are conducted at baseline and week 6 of radiotherapy, then at 4 weeks, 3 months and 6 months after radiotherapy completion: MD Anderson Dysphagia Inventory score (MDADI) and quality of life questionnaires (EORTC QLQ-C30 and H&N43). Adverse events will be assessed, using CTCAE v5.0 [48], at baseline and weekly during radiotherapy until 4 weeks post completion, then at 3 and 6 months post radiotherapy. An optional sub-study will collect blood and saliva samples at baseline, weekly during radiotherapy and at week 4, then 3 and 6 months post radiotherapy. A further optional procedure for participants is to undergo a research biopsy from the primary tumour after ten fractions of radiotherapy (after MRI_2).1.CTCAE v5.0 will be used to grade acute toxicity, RTOG Radiation Morbidity Scoring Criteria will be used to grade late toxicity, at 3 & 6 months post completion of RT2.Quality of Life questionnaires include EORTC QLQ-C30 & H&N43

**Table 3 t0015:** –Schedule of assessments.

Study assessment	Baseline	RT Week 1	RT Week 2	RT Week 3	RT Week 4	RT Week 5	RT Week 6	Post-RT Week 1	Post RT week 2	Post RT week 3	Post RT week 4	Post RT 3 monts	Post RT 6 months
Performance status ECOG	X						X				X	X	X
Swallowing assessment (MDADI)	X						X				X	X	X
Toxicity review^1^	X	X	X	X	X	X	X	X	X	X	X	X	X
QoL Questionaires^2^	X						X				X	X	X
Translational blood & saliva sample	X	X	X	X	X	X	X				X	X	X
Research biopsy				X									

Loco-regional control rates at 12 and 24 months, as well as overall survival will also be collected from record review. Safety reporting will be carried out by the Pharmacovigilance Department of the Glasgow Oncology Clinical Trials Unit.

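### The safety endpoint is Grade 3+ toxicity, but the planned comparison counts only grade III or IV RT-related events, so a patient whose only severe event is grade 5 scores as having none

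*Protocol article*

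**What the plan says.** The protocol article describes the severe-toxicity comparison twice.

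- **Section 2.5, Secondary Endpoints**, reads: "Proportion of Grade 3+ acute (up to 3 months) and early late (3–6 months) toxicity rates, comparing dose-escalated and standard radiotherapy cohorts". The grade is open at the top, there are two time windows, and no attribution condition is stated.
- **Section 2.6, Statistics**, reads: "the proportion of dose escalated patients experiencing grade III or IV RT-related toxicities will be compared with standard treatment patients". The grade is capped at IV and events must be RT-related. The effect measure is an odds ratio, given with its exact 95% interval.

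On data collection, section 2.5 states: "Adverse events will be assessed, using CTCAE v5.0 [48], at baseline and weekly during radiotherapy until 4 weeks post completion", with further reviews at 3 and 6 months. No attribution filter is attached to this. On scales, the notes to the assessment schedule say: "CTCAE v5.0 will be used to grade acute toxicity, RTOG Radiation Morbidity Scoring Criteria will be used to grade late toxicity".

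Deaths are handled elsewhere in section 2.6: "Overall survival and cancer-specific survival will also be summarised at 6-months follow-up". Section 2.5 also assigns safety reporting to the trials unit's pharmacovigilance department. The planned size is 20 patients in total.

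**The concern.** The two sentences describe the same cohort comparison with different definitions of a case. An analyst who follows section 2.6 does not estimate the endpoint in section 2.5. The difference lies at the severe end: 3+ admits grade 5, while III or IV does not.

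This odds ratio is the article's planned comparison of severe toxicity between escalated and standard treatment. The Introduction says that intensifying an already morbid regimen needs careful consideration, and reports that over half of the regional oropharynx cancer population studied was moderately or severely frail. A severe-toxicity count that omits fatal toxicity is a poor summary in that setting. If the choice between definitions is left until events are known, it also becomes a data-driven choice.

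**Working it through.** The article gives no toxicity rate, cohort split or computed figure for this comparison, so there is nothing to reproduce. The check sets the texts side by side and then illustrates the effect on assumed counts.

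**1. The two definitions**

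| Element | Section 2.5 (endpoint) | Section 2.6 (analysis) |
|---|---|---|
| Grade | 3 and above | III or IV |
| Attribution | none stated | RT-related |
| Windows | acute to 3 months; early late 3–6 months | not repeated |
| Measure | proportion, by cohort | proportion, odds ratio with exact 95% CI |

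The first row is a contradiction. The second is a difference in wording that may or may not be one in meaning. The third is silence.

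**2. Who is affected**

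A patient with a recorded RT-related grade III or IV event who later dies of toxicity is a case under both rules. The rules part for a patient whose only qualifying event is grade 5: a case under section 2.5, not a case under section 2.6. This takes grade 5 to mean death from the event, the ordinary meaning of the scale, which the article does not define.

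**3. Illustration on assumed counts**

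The total of 20 is from section 2.6; the split and the counts are assumptions. With *a* cases among *m* escalated patients and *b* cases among *n* standard patients, the sample odds ratio is

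OR = a(n − b) / [b(m − a)].

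Intervals are conditional exact 95%.

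For 10 v 10, with grade 3–4 events in 5 v 4:

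- Section 2.6 rule: (5 × 6)/(4 × 5) = 30/20 = 1.50 (0.19 to 12.4).
- One escalated grade-5-only patient added, 6 v 4: (6 × 6)/(4 × 4) = 36/16 = 2.25 (0.28 to 19.2).
- Two added, 7 v 4: (7 × 6)/(4 × 3) = 42/12 = 3.50 (0.41 to 33.3).
- One added in the standard cohort instead, 5 v 5: (5 × 5)/(5 × 5) = 1.00. The omission can therefore act in either direction.

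Other splits, with one escalated patient added:

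- 8 v 12, 5 v 4 becoming 6 v 4: (5 × 8)/(4 × 3) = 3.33 becomes (6 × 8)/(4 × 2) = 6.00; intervals 0.37 to 32.3 and 0.60 to 80.0.
- 12 v 8, 5 v 4 becoming 6 v 4: (5 × 4)/(4 × 7) = 0.71 becomes (6 × 4)/(4 × 6) = 1.00; intervals 0.08 to 6.1 and 0.12 to 8.4.

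One patient visibly moves the point estimate. In each of these one-patient comparisons both intervals include 1 and are too wide to say much about relative harm.

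**The case against.** The strongest case on the other side has five parts.

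- **A toxic death is not lost from the report.** A reader might infer that a fatal event vanishes. It does not: overall and cancer-specific survival are summarised at 6 months with Kaplan-Meier plots and log-rank tests, and safety reporting is separate. This stands. What is lost is its place in the toxicity odds ratio; a survival curve does not by itself identify a death as toxicity.
- **The affected group is small.** Weekly review to 4 weeks after radiotherapy makes a fatal toxicity with no earlier grade 3–4 record less likely, though still possible, particularly between later visits. This stands as a limit on size.
- **RT-related may only clarify the word toxicity.** That reading is fair, since late events are graded on a radiation morbidity scale. A reader might go further and infer that clinicians who know the cohort will attribute events and bias the comparison. The article does not say who attributes events or whether they know the cohort, and a condensed article commonly leaves this to the full protocol. Only the difference in wording stands.
- **The windows are not dropped.** A reader might infer that section 2.6 pools acute and early late events. It does not say so, and section 2.5 already fixes the windows. Not repeating them in a short paragraph is no contradiction.
- **Little hangs on this odds ratio.** The primary endpoint is feasibility, and no test, threshold or decision rule is attached to the toxicity comparison. This stands and limits the severity.

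None of this removes the grade mismatch. Even if III or IV was meant as shorthand for severe, the written rule excludes grade 5.

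**Conclusion.** The concern holds for the case definition. Section 2.6 caps at grade IV an endpoint that section 2.5 leaves open, and applied literally it scores a patient with only a grade 5 event as free of severe toxicity. The attribution wording also differs and should be aligned, but it is the weaker part.

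Severity is moderate. The comparison is secondary and non-randomised, in 20 patients. On the assumed 10 v 10 counts, one such escalated patient is the difference between odds ratios of 1.50 and 2.25, with intervals that are uninformative either way. The contradiction itself depends on none of the assumed counts. The documents do not support the stronger conclusions that fatal toxicity would go unreported or that the comparison is biased by attribution made with knowledge of the cohort.

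**What to change.** Use one definition in both sections.

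1. In section 2.6, replace the grade III or IV wording with grade 3 or higher (grades 3 to 5), reported in the acute and early late windows already defined in section 2.5.
2. List grade 5 events individually, by cohort.
3. Align the attribution wording. Because section 2.5 sets no attribution condition, one option is to report Grade 3+ events of any attribution, with the RT-related subset alongside. If the RT-related restriction is what was intended, state it in section 2.5 as well.

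Settle this before the toxicity data are compared by cohort. The cost is about a sentence of text plus a short listing. Toxicity is already graded at each scheduled review, so no extra visits are needed. Reported severe-toxicity rates may be slightly higher than under the present wording.

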## Introduction and background

1

Head and neck cancer is the 9th most common cancer in the UK, with 12,800 new cases annually, and numbers expected to rise to 16,300 by 2040 [1]. Increasing numbers of patients with oropharyngeal squamous cell cancer (OPSCC) is not only due to the well documented growing incidence of the Human Papillomavirus (HPV), but also due to an increase in HPV-negative cancers [2]. Between 2010 and 2020, the rate of OPSCC increased by a factor of 2·1, and this is projected to more than double between 2020 and 2039 [3]. Survival is known to be favourable with HPV-positive disease, with a 3 year survival of 93%, leading to the consideration of possible treatment de-escalation [4], [5]. However, patients with HPV-negative cancers, and those with a substantial smoking history regardless of tumour HPV status, have poorer survival outcomes, with a 3 year overall survival as low as 46.2% [4], [6]. While HPV-negative and HPV-positive disease are different entities, prognosis is affected by smoking history in addition to tumour HPV status. Poorer outcomes, compared to the HPV-positive non-smoking population, is seen in both groups, with a common unmet need to improve disease control and survival. With a plethora of negative studies examining uniform de-intensification for HPV-positive OPSCC there is now acceptance that a more personalised approach to de-escalation of treatment is required [7], [8], [9], [10]. For example, promising results have been demonstrated in the Phase II setting using 18F- fluoromisonidazole Positron Emission Tomography (F-MISO PET) to guide hypoxia-directed dose de-escalated radiation [11]. Attempts to uniformly intensify treatment in the poorer prognosis populations have similarly been unsuccessful to date, both in the oropharyngeal [12] and non-oropharyngeal sub-sites [13]. An imaging biomarker to guide intensification of treatment for the poorer prognosis population remains an urgent unmet need.

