Standard treatment for locoregionally advanced oropharyngeal cancer is 6–7 weeks of chemoradiotherapy with platinum-based chemotherapy [14]. Considering poorer outcomes, it is important that patients with HPV-negative OPSCC receive this standard of care treatment, however there are often associated factors that preclude the chemotherapy component. Socioeconomic deprivation and HPV-negative disease [15] are knowingly linked, as well as a history of smoking and/or alcohol, often leading to multimorbidity. These factors can affect performance status and suitability for concurrent treatment [16], [17], [18]. In addition, the benefit of cisplatin is not seen in patients aged 70 years old or older, and the average age at diagnosis with HPV-negative disease is 66 years [19]. Recent data has shown as many as 41% of patients are receiving single modality radiotherapy, despite having indications for concurrent chemotherapy [20]. UK guidelines recommend that concomitant cisplatin with curative radiotherapy is offered to patients who are ‘young and fit enough’ to tolerate the likely increased toxicity. [21]. Recent work evaluating fraily in the oropharynx cancer population in our region found that over half of patients were categorised as moderately or severely frail, [22] giving an insight to the challenges in delivering optimal treatment. This may contribute to poorer outcomes [23], [24], and highlights the clinical need for an alternative, intensified radiotherapy approach.

Intensifying an already morbid treatment regime, in a patient population that is often unsuitable for standard of care treatment, needs to be carefully considered. Yet, as the pattern of treatment failure is predominantly inadequate loco-regional control in both HPV-positive and negative disease, radiotherapy dose-escalation is an enticing option [4]. A dose-response relationship in head and neck squamous cell cancer (HNSCC) is recognised, however escalating dose clinically has revealed mixed results. Increasing dose can result in increased toxicity rates [25], with other studies showing frequency and severity of toxicities remaining similar [26]. Of note, these studies, along with the ones described earlier, have uniformly increased treatment to all poor prognosis patients. Intensifying treatment only for those who really need it, i.e. those tumours predicted to respond inadequately to standard treatment, allows the risk of increased toxicity to be limited to the sub-group most in need.

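### Loco-regional control is analysed as a yes/no count at 6 months, which neither reaches the endpoint's own 12- and 24-month times nor separates death without relapse from loco-regional failure

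*Protocol article*

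**What the plan says.** Section 2.6 (Statistics) of the protocol article sets the analysis of loco-regional control: "The number of patients achieving loco-regional control at 6-months follow-up will be reported, along with an odds ratio for the comparison of groups", with an exact 95% confidence interval. The next sentence gives a time-to-event presentation to the two survival endpoints only: "Overall survival and cancer-specific survival will also be summarised at 6-months follow-up, presented with Kaplan-Meier plots", with log-rank tests.

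Section 2.5 places the same endpoint at other times. The secondary endpoints list reads "Loco-regional control rates at 12 and 24 months, overall survival, and cancer specific survival; comparing dose-escalated and standard radiotherapy cohorts". The text under the assessment schedule gives the source of the data: "Loco-regional control rates at 12 and 24 months, as well as overall survival will also be collected from record review".

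The Introduction describes the setting. Patients with HPV-negative disease or a substantial smoking history "have poorer survival outcomes, with a 3 year overall survival as low as 46.2" per cent. In the region's oropharynx cancer population, "over half of patients were categorised as moderately or severely frail".

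The article does not say how a patient is counted who dies without loco-regional relapse, or is lost, before the time point.

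**The concern.** Loco-regional control is a statement about the tumour in the neck and throat. A count at a fixed date has two cells per cohort, and four kinds of patient must fit into them: alive and controlled, relapsed, dead without relapse, and not followed that far. The first two fit. The other two do not, and the published figure depends on where they are put.

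A patient who died of comorbidity at month 4 with no relapse did not, on a literal reading, achieve control at 6-month follow-up. Scoring that patient as not controlled turns the measure into survival free of loco-regional failure. Leaving the patient out removes early deaths selectively. In a frail group with poor survival, both choices mix general mortality into a measure of tumour control.

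This endpoint matters because the Introduction names inadequate loco-regional control as the main pattern of failure and the reason for considering dose escalation. It is the efficacy measure closest to the trial's rationale. The method given in Section 2.6 also stops at 6 months, before either time named in Section 2.5. Deaths accumulate between those times, so the question of how they are counted carries more weight there.

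**Working it through.** The article gives no numerical figure for loco-regional control, so there is none to reproduce. The check is how far the result depends on the unstated counting rule.

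**Inputs from the article.** Target sample 20 (Section 2.6). Radiotherapy over six weeks, about 1.4 months (Section 2.4). 3-year overall survival as low as 46.2% (Introduction; a background figure, not a trial assumption). Times of 6 months (Section 2.6) and 12 and 24 months (Section 2.5).

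**Assumptions not in the article.** Constant hazard; survival counted from the start of radiotherapy and the time points from its end; 25 to 50% of deaths occur without loco-regional relapse.

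**Step 1, deaths.** Hazard = −ln(0.462)/3 = 0.257 per year. Proportion dead by t = 1 − exp(−0.257 t), with t = (6, 12 or 24 + 1.4)/12 = 0.617, 1.117 or 2.117 years.

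**Step 2, effect of scoring deaths as failures.** The understatement of control is the proportion dead × 0.25 to 0.50.

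| Time after radiotherapy | Dead | Of 20 | Dead without relapse, of 20 | Understatement, points |
|---|---|---|---|---|
| 6 months | 14.7% | 2.9 | 0.7 to 1.5 | 3.7 to 7.3 |
| 12 months | 25.0% | 5.0 | 1.2 to 2.5 | 6.2 to 12.5 |
| 24 months | 42.0% | 8.4 | 2.1 to 4.2 | 10.5 to 21.0 |

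If all times are counted from baseline, deaths are 12.1%, 22.7% and 40.2%, and the understatement is 3.0 to 6.0, 5.7 to 11.3 and 10.1 to 20.1 points. If 3-year survival were 70% (an assumption), with the clock as in the table, it is about 2 to 4, 3 to 6 and 6 to 11 points. If 75% of deaths were without relapse, the upper ends counted from baseline rise to 9, 17 and 30 points.

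**Step 3, the three counting rules side by side.** Assume a cumulative loco-regional failure of 20% at each time, so that 1 minus cumulative incidence is 80%. Write d for the proportion dead without relapse (Step 2).

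- Deaths counted as relapse-free, follow-up complete: 80%, the intended quantity.
- Deaths scored as failures, 0.80 − d: 73 to 76% at 6 months, 68 to 74% at 12, 59 to 70% at 24.
- Deaths excluded, (0.80 − d)/(1 − d): 78 to 79% at 6 months, 77 to 79% at 12, 75 to 78% at 24.

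**Step 4, direction of the bias in the odds ratio.** Take 20% failure in both cohorts, so the true odds ratio is 1. Suppose death without relapse is 5% in one cohort and 15% in the other. Scored as failures, control is 0.75 and 0.65, and the odds ratio is (0.65/0.35)/(0.75/0.25) = 0.62. With the death rates swapped it is 1/0.62 = 1.62. Suppose instead that failure differs, 10% against 30%, and death without relapse is 10% in both. The odds ratio then falls from (0.9/0.1)/(0.7/0.3) = 3.86 to (0.8/0.2)/(0.6/0.4) = 2.67. The bias can run towards or away from 1. Cohorts are formed by change in ADC and not by randomisation, so equal death rates cannot be presumed.

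**Step 5, scale against chance.** If 20 patients split 10 and 10 with 8 controlled in each, the exact 95% interval for the odds ratio is 0.06 to 17.1.

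**The case against.** The strongest reply is that the article states no scoring rule. A reader might infer from Section 2.6 that deaths without relapse are scored as failures, or that exclusion is the only alternative. The article supports neither inference. Such a patient can be counted as having no loco-regional failure, and with complete follow-up that count equals 1 minus the cumulative incidence. A coding rule of this kind often sits in the full protocol or analysis plan, which are not shown. This stands: the miscount is a risk and not a stated fact.

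It also stands that the count is written for 6 months only. The 12- and 24-month figures above therefore assume that the same count is carried forward. At 6 months at most one or two patients are affected, on a pessimistic survival figure, and chance variation at 20 patients is far larger than the bias.

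Two further inferences should be resisted. One is that the odds ratio is always pulled towards 1; Step 4 shows otherwise. The other is that the predictive values quoted in the Introduction can serve as control rates for the two cohorts. They come from an earlier study of ADC change and concern long-term disease control. In this trial the non-responders receive the escalated plan.

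Nor does the article make loco-regional control the basis for going on. The primary endpoint and its threshold concern completion of the adapted treatment, and deaths remain visible in the survival analyses.

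What the reply does not remove is that Section 2.6 goes beyond silence on a coding rule. It commits to a count and an odds ratio at 6 months, while the endpoint is set at 12 and 24 months and the neighbouring survival endpoints get time-to-event methods. Even the favourable reading fails once a patient is lost to follow-up.

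**Conclusion.** The concern holds as a weakness in a stated method, not as a demonstrated miscount. The yes/no count at 6 months does not reach the times in Section 2.5, and it does not distinguish loco-regional failure from death without failure or from incomplete follow-up. One of the three possible counting rules gives the intended quantity, and only when follow-up is complete.

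The effect is about 0 to 2 of 20 patients at 6 months. It would be about 6 to 12 points at 12 months and 10 to 21 points at 24 months if deaths were scored as failures there. Those later figures rest on a constant hazard, the low-end background survival of 46.2%, and a 25 to 50% share of deaths without relapse that the article does not give. The direction of any bias in the odds ratio is unknown. The primary endpoint and the sample size are not affected. This is a cheap improvement to a secondary endpoint.

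**What to change.** In Section 2.6, replace the count and odds ratio as the main analysis of loco-regional control with the cumulative incidence of loco-regional failure. Estimate it by the Aalen-Johansen method, with death without loco-regional failure as a competing event and patients lost to follow-up censored. Report it with 95% confidence intervals at 12 and 24 months, and at 6 months if that time is kept, overall and by cohort. This also brings Section 2.6 into line with Section 2.5.

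Beside it, tabulate at each time the number alive and controlled, the number with loco-regional failure, and the number dead without failure. If a between-cohort odds ratio is kept, label it descriptive and show deaths without relapse separately.

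The cost is a change of wording and a little analysis code. Dates of loco-regional failure and death should be obtainable from the record review that Section 2.5 already plans. The downsides are wide intervals at 20 patients and a presentation slightly less simple than a count.
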